**Study protocol Modify Description**

| Modify item/page/line number | Original contents- the protocol for ethics review (V1.1.1) | Modified contents-the protocol manuscript |
| --- | --- | --- |
| Study method-standard anesthesia management/Page10/line10 | Intraoperative anesthesia can be maintained by intravenous anesthesia or combined with intravenous anesthesia, | Anesthesia will be then maintained with combined intravenous anesthesia and inhalational anesthesia. |
| Study method-standard anesthesia management/Page10/line11 | and the intraoperative BIS will be maintained between 40 and 60. | to maintain the BIS value between 40 and 50. |
| Study method-standard anesthesia management/Page10/line26 | H3 receptor blocker (Tropisetron 5mg) will be administered before end of surgery to prevent nausea and vomiting. | Not mentioned. |
| Study method-statistics analysis for primary outcome /page15/line26 | The Student’s t test for primary outcome analysis | Student t test or the Mann-Whitney U test, the multiple linear regression model or two-way analysis of covariance will be applied to account for potential confounders. |
| Study method-statistic analysis for missing data/page15 | Not mentioned | Missing data will be imputed using the worst-case scenarios and last observation carry forward method. |
| Study method-statistic analysis/page4/line14 | Event time data will be analyzed using Kaplan-Meier survival analysis, and differences among groups were assessed using log-rank test and proportional risk regression models. | Not time-to-event analysis. |
| Secondary Outcome assessments/Page19/line20 | Calculated blood loss: Calculated blood loss = estimated blood volume×(Hcti−Hctf)+transfused RBC volume]/Hctmean. | Calculated blood loss is assessed by the formula：  Calculated blood loss (CBL) = estimated blood volume×(Hcti−Hctf)+transfused RBC volume]/Hctmean  Estimated blood volume for women=[weight (kg)^0.425 × height (cm)^0.725 ] × 0.007184 × 2217+age (years) × 106  Estimated blood volume for men =[weight(kg)^0.425 x height (cm)^0.725 ]× 0.007184 x 3,064-825 |
| Intervention/page9/line25 | TXA continuous infusion of 5mg/kg/h until the end of the operation | TXA continuous infusion of 5mg/kg/h until dural closure |

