Meningiomas are the most common intracranial tumors, accounting for more than 30%[1]. Although the nature of meningioma is mostly benign, due to its occupying effect and invasion of blood vessels, meningioma patients are often accompanied by severe intracranial pressure elevation, encephaledema, and cranial nerve injury, and thus lead to serious neurological dysfunction. Huge meningiomas, defined as diameter ≥5cm, account for about 11% of primary intracranial neoplasm[2]. surgical resection of huge meningiomas is the preferred treatment to improve neurological outcomes. However, most of the huge meningiomas are accompanied by a rich blood supply, compressing and/or distorting blood vessels in their growth process. Some of the meningiomas also surround peripheral blood vessels and involve the venous sinuses, invading the scalp and skull, and the blood loss during resection could be as high as 4000mL[2]. Besides that, the tissue plasminogen activator in tumor and peritumoral brain tissues can induce fibrinolysis and contribute to intraoperative hemorrhage[3]. Massive intraoperative bleeding and severe hemodynamic fluctuations during the resection of huge meningioma may lead to organ injury, coagulopathy and even be life-threatening[4, 5]. Therefore, perioperative blood management of huge meningioma resection is challenging.

There are many techniques for perioperative blood management in neurosurgery, but each blood management technique is accompanied by certain deficiencies and a heavy economic burden. Even with all of the above blood management methods, allogenic transfusion is inevitable in some cases due to excessive blood loss, while allogenic transfusion presents a high risk of immunosuppression, hemolysis, postoperative infection, and transfusion-related lung injury, resulting in prolonged hospital stay and even death[6-10].

Tranexamic Acid (TXA) is a synthetic antifibrinolytic drug with a lysine-like structure. TXA can inhibit plasminogen activation and prevent plasminogen from binding to fibrin, thus blocking the fibrinolytic process, preventing thrombolysis, reducing bleeding, and reducing the blood transfusion rate[11, 12].

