**2. Sample size and study project**

According to previous studies, the intraoperative blood loss for huge meningioma was about 1000ml, and the overall standard deviation of the population was about 400ml. A single TXA infusion was assumed to be effective in reducing blood loss by about 25%, and continuous TXA infusion could further reduce blood loss by 25%, so the minimum effect size was 250ml. A sample size of 228 patients (76 per group) is calculated to provide 90% power to detect the between-group difference at a significance level 𝛼 of 0.017 and the overall type I error of 0.05, with a dropout rate of 2.5% with Bonferroni adjustment.

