**Follow-up items:** examination (blood routine, coagulation function and chemistry panel) on the first day after surgery, Caprini risk score on the first day after surgery, KPS score on postoperative day 1, day 3, day 5 ±2 and at discharge and on 180 days. Others include GCS score and complication evaluation.

1. **Outcome assessments**

The primary outcome is the estimated cumulative intraoperative blood loss, which is calculated using the formula: collected blood volume in the suction canister (mL) – the volume of flushing (mL) + the volume from the gauze tampon (mL).

The secondary outcomes include:

1. Intraoperative coagulation function monitoring assessed by rapid TEG at the beginning and the end of the operation.
2. Calculated blood loss: Calculated blood loss = estimated blood volume×(Hcti−Hctf)+transfused RBC volume]/Hctmean.
3. Intraoperative cell salvage use and allogeneic blood products use. The indications for routine blood transfusion in our institution are as follow:

**a.** Hb < 9g/dl or Hct < 30%. If the intraoperative pathology consultation indicated a WHO classification of II or I, we will first consider cell salvage. If intraoperative pathology was unavailable or WHO classification > II, allogeneic blood transfusion will be preferred.

**b.** Use of frozen plasma, cryoprecipitate, and platelet products, will be initiated based on the American Society of Anesthesiologists Task Force on Blood Component Therapy: PT/APTT is more than 1.5 times prolonged, fibrinogen <1g/L, or diffuse microvascular bleeding at the surgical field (although there is no surgical hemostasis and/or no visible clots in the surgical field).

1. Simpson grading system for the extent of meningioma resection.
2. Hemostasis: Hooda score.
3. Operative field surgical hemostasis score using VAS score.

Safety outcome includes 1) frequency and episodes of postoperative seizure; 2) other intraoperative complications (allergy, hypoxemia, refractory hypotension, pulmonary embolism, etc.) other postoperative complications (venous thrombosis, new cerebral ischemia, intracranial hematoma, hydrocephalus, infection, abnormal renal function, myocardial infarction).

Economic outcome: 1) ICU admission, length of ICU stays; 2) length of hospital stay and hospital charge.

1. **Potential risks, benefits of the project & risk management**

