The audit team will assess the research progress, ensure the investigator and patient follow the protocol, and resolve urgent issues through regular site visits, letters, or phone calls. During these visits, the audit team and the principal investigator will jointly supervise the following key points: informed consent, recruitment and follow-up, and documentation and reporting of SAEs.

1. **Data preservation**

All data will be recorded in the paper CRF, which will be kept in the department's locked filing cabinet for at least 5 years. Both original and nature language data are encoded for data storage, review, tabulation, and analysis. The data will be securely entered and stored in an electronic database. Double data entry will be used.

1. **Data monitoring committee**

The Data Monitoring Committee (DMC) will be composed of experts in anesthesiology, ethics, statistics and methodology, as an independent body to monitor the safety, efficacy, ethical issues, and progress of the trial. The DMC will conduct audits through regular interviews or telephone calls. DMC reserves the right to review recruitment process at any time. The audit process will be independent.

1. **Statistics**

Sample size and statistical power: According to previous research reports, the intraoperative blood loss for huge meningioma was about 1000ml, and the standard deviation of the population was about 400ml. A single TXA infusion effectively reduced the amount of blood loss by about 25%, and continuous TXA infusion further reduced the amount of blood loss by 25%. Therefore, the estimated effect size is 250ml. A sample size of 228 patients (76 per group) is calculated to provide 90% power to detect the between-group difference at a significance level 𝛼 of 0.017 and the overall type I error of 0.05, with a dropout rate of 2.5% with Bonferroni adjustment.

1. Statistical analysis principle: Intention-to-treat analysis.
2. The Student’s t-test will be used to compare the primary outcome between groups, and a p-value <0.017 will be considered as a significant difference between the two groups. The overall p-value<0.05 was considered as a significant difference in blood loss among the three groups.

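### The single missing-data rule (worst case and LOCF) does not fit the primary outcome: LOCF cannot act on a one-off blood-loss value, and an undefined worst-case value biases the mean difference when missingness is unequal and inflates the SD

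*Protocol*

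**What the plan says.** The Statistics section of the protocol body gives no method for missing data. The modification table at the end (Study protocol Modify Description) has a row for it. The ethics-review column is empty on the subject, and the modified column reads "Missing data will be imputed using the worst-case scenarios and last observation carry forward method". This is the later text and the only missing-data rule in the document.

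Under Outcome assessments: "The primary outcome is the estimated cumulative intraoperative blood loss, which is calculated using the formula" suction volume minus flushing volume plus gauze volume. That gives one figure per patient, fixed at the end of surgery.

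The Statistics section sets intention-to-treat as the principle. It names Student's t-test for the primary outcome, and "a p-value <0.017 will be considered as a significant difference between the two groups". A later item in the same section, and the modification table, also allow Mann-Whitney; the table adds linear regression or analysis of covariance. The sample-size paragraph assumes "the intraoperative blood loss for huge meningioma was about 1000ml", "the overall standard deviation of the population was about 400ml", "so the minimum effect size was 250ml", and 76 per group "with a dropout rate of 2.5% with Bonferroni adjustment".

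**The concern.** The point is the rule itself, not a difference between the table and the body. One sentence covers all missing data, so on its face it covers a missing blood-loss value under intention-to-treat. For that outcome half of the rule is empty, because there is no earlier observation to carry forward. The other half enters an extreme constant as though it had been measured.

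In a comparison of means this does two things. It adds artificial variance in any arm with missing values. It also moves that arm's mean upward, so unequal missingness biases the estimated effect: against TXA if the missing values are in a TXA arm, in favour of TXA if they are in the control arm. The rule therefore cannot be defended as uniformly conservative. Because the worst value is undefined, its choice is left open and could be made after the data are seen.

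The Blinding paragraph contains one non-random route to missing data: a participant unblinded after a life-threatening event is dropped. Such events could differ by arm.

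For outcomes measured repeatedly, such as Karnofsky score and complications, LOCF could carry an early postoperative status to day 180.

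**Working it through.** **Inputs.** From the sample-size paragraph: means 1000 and 750 mL, SD 400 mL, 76 per arm, alpha 0.017 (taken as two-sided, which the protocol does not state), dropout 2.5%. Assumed: 2 missing per arm (2.5% of 76 = 1.9); worst value = the largest value observed in the two arms compared; normal data.

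**The plan's own figure.** n per arm = 2(z₁₋α/₂ + z₁₋β)² SD²/δ² = 2 × (2.387 + 1.282)² × 400²/250² = 68.9, so 69. Dividing by 0.975 gives 71 per arm, 213 in total. An exact t calculation gives 71, then 73 per arm, 219 in total. The stated 76 is matched if a Mann-Whitney allowance is added (70/0.955 → 74; 74/0.975 → 76), though the protocol does not mention one. With 74 evaluable per arm, exact t-test power is 91.6%. The 228 does not depend on the imputation rule.

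**Effect of a worst value W in a fraction m of an arm.**
- Mean = (1 − m)μ + mW
- Variance = (1 − m)SD² + m(1 − m)(W − μ)²

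With m = 2/76 = 0.0263, and W about 1980 mL (the average largest observed value in simulation under the plan's effect):

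- Balanced, 2 + 2: difference = 250 × 74/76 = 243.4 mL, a shift of 6.6 mL. Control SD = √(0.9737 × 400² + 0.0256 × 980²) ≈ 425 mL. TXA SD = √(0.9737 × 400² + 0.0256 × 1230²) ≈ 441 mL.
- TXA arm only: TXA mean = (74 × 750 + 2 × 1980)/76 = 782 mL, so the difference is about 218 mL.
- Control arm only: control mean = (74 × 1000 + 2 × 1980)/76 = 1026 mL, so the difference is about 276 mL.
- No true effect, 4 missing in one arm only (W about 2060 mL): false difference = 4/76 × (2060 − 1000) ≈ 56 mL.

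**Simulated t-test results** (20,000 trials per row, alpha 0.017):

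| Missing (control + TXA) | Value used | Mean difference | Rejection rate |
|---|---|---|---|
| 2 + 2 | none, observed only | 250 mL | 92% |
| 1 + 1 | worst observed | 247 mL | 90% |
| 2 + 2 | worst observed | 243–244 mL | 87–88% |
| 0 + 2 | worst observed | 217–218 mL | 79% |
| 2 + 2 | 4000 mL | 243–244 mL | 46% |
| 0 + 2 | 4000 mL | 164 mL | 22% |
| 4 in one arm only, no true effect | worst observed | 56 mL (false) | 4% (nominal 1.7%) |
| 4 in one arm only, no true effect | 4000 mL | 158 mL (false) | 10% (nominal 1.7%) |

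**Mann-Whitney on the same data.** Power is about 90% on observed values. With 2 + 2 missing it is 87–89% at the worst observed value and 88% at 4000 mL. With 0 + 2 missing it is about 82–83% at either value. With no true effect and 4 missing in one arm only, type I error is about 2.5–3%.

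**The case against.** The strongest reply is that the sentence is general. It can be read as LOCF for repeated measures and worst case for the rest, with details left to a statistical analysis plan that is not shown. Part of that stands. A reader might infer that the protocol assigns LOCF to blood loss; it does not say so. What remains is that the document does fix the methods, exempts nothing, and under intention-to-treat leaves only the worst-case half to act on a missing primary value. Entering a worst-case value as observed is a poor rule for that outcome, and more detail would not repair it.

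A reader might also infer a collapse in power to 46% or 22%. The document does not support that. Those figures need 4000 mL to be imputed and a t-test to be used. The Background says "the blood loss during resection could be as high as 4000mL", but only as a description of the disease, and nothing designates it as an imputation value. Mann-Whitney, which is also allowed and would be the likelier choice for skewed data, keeps about 88% and 83% in the same two cases. It reduces the harm from inflated variance but does not remove bias from unequal missingness.

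The 2.5% is a dropout rate, not a rate of missing blood-loss values. The volume is recorded in theatre, so a patient lost later will normally have one. Two missing per arm is therefore probably on the high side.

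The day-180 point is secondary. None of the listed secondary outcomes is set at 180 days, and monitoring for TXA adverse effects runs to day 5. LOCF still reaches the day-180 assessments that the protocol schedules.

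**Conclusion.** The concern holds as a defect in a stated rule, of moderate size. LOCF has no role for the primary outcome. Worst-case values are undefined and unsuited to a primary comparison of means. With balanced loss of 2 per arm at the worst observed value, the cost is 4 to 5 points of t-test power and a shift of 6 to 7 mL; with equal missingness and no true effect there is no bias. The more serious case is unequal missingness: 2 values missing in one TXA arm only cost about 32 mL of the 250 mL difference and about 13 points of power, and 4 missing in one arm only raise type I error to about 4%.

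These sizes rest on the plan's means and SD, normal data, two-sided alpha 0.017, the assumed numbers missing and the worst observed value as the imputed one. The larger losses hold only with an extreme imputed value and a t-test. The change should be made because it is cheap and closes an open choice before unblinding, not because the trial's power is likely to be lost.

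**What to change.** Replace the sentence with a rule by outcome:

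- **Primary analysis:** all randomised patients with an observed blood loss, analysed in the arm assigned. This includes anyone unblinded or withdrawn whose volume was recorded.
- **Supporting analysis:** multiple imputation under missing-at-random, using recorded baseline and intraoperative data as predictors (for example tumour size and preoperative haematocrit).
- **Sensitivity analysis:** worst-case imputation only under that label, with the value defined in advance, or a tipping-point analysis. Report the number missing and the reason, by arm.
- **LOCF:** delete it, and do not carry an earlier status forward to day 180.

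The cost is protocol or analysis-plan wording and a little programming. No patients or measurements are added, and the sample size does not change. The wording should be settled before unblinding.
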